#### Sample size

This is an exploratory pilot trial, and the sample size of 24 participants (12 per group) is based primarily on feasibility considerations and is consistent with recommendations for pilot studies in neuromodulation and SCI rehabilitation (Julious, 2005). This sample size is sufficient to estimate the standard deviation of the primary outcome, assess feasibility parameters, and generate preliminary effect size estimates with reasonable precision to inform the power calculation for a subsequent confirmatory trial. Assuming 20% attrition, we aim to enroll 24 participants to ensure at least 10 evaluable participants per arm. This is consistent with sample sizes in comparable neuromodulation pilot trials in SCI (Feng et al., 2023; Gharooni et al., 2018; Lin et al., 2023).

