### Randomization and allocation concealment

Participants will be randomized in a 1:1 ratio using a computer-generated, permuted block randomization schedule (block sizes of 4 and 6, randomly varied) stratified by AIS grade (C versus D) and baseline UEMS on the more impaired side (10–14 versus 15–20). The randomization schedule will be generated by an independent biostatistician at the Clinical Research & Innovation Office, Tan Tock Seng Hospital, with no direct involvement in participant recruitment or assessment, and stored in a secure, web-based centralized randomization system (REDCap Randomization module). Allocation concealment will be ensured by sequential, opaque, sealed envelopes accessible only to the unblinded intervention therapist.

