### Outcome measures

#### Primary outcome

The primary outcome is the change in Upper Extremity Motor Score (UEMS) from baseline (week 0) to post-intervention (week 12). The UEMS is a component of the International Standards for Neurological Classification of Spinal Cord Injury (ISNCSCI) examination and assesses the strength of 10 key muscles of the upper extremities (5 per side) on a 0 to 5 scale, yielding a score of 0 to 25 per side or 0 to 50 bilaterally. The UEMS has well-established psychometric properties, is sensitive to change in SCI populations, and was used as a primary or secondary endpoint in the Up-LIFT trial and other major SCI neuromodulation studies (Moritz et al., 2024; Singh et al., 2024).

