##### Feasibility outcomes

As this is a pilot study, pre-specified feasibility outcomes will be evaluated against the following progression criteria: (1) recruitment rate of at least 2 participants per month; (2) retention rate of 80% or higher (i.e., at least 20 of 24 participants completing the study); (3) intervention adherence of 83% or higher (i.e., at least 20 of 24 sessions completed); (4) assessment completion rate of 90% or higher for the primary outcome; and (5) no serious adverse events attributable to the combined intervention. These criteria will determine whether progression to a full-scale confirmatory trial is warranted.

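### At the assumed 20% attrition, 24 enrolled gives an expected 9.6 evaluable per arm, not an assured 10, and the same rate sits at the retention progression limit

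*Protocol article*

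**What the plan says.** The Sample size section describes an exploratory pilot and says that "the sample size of 24 participants (12 per group) is based primarily on feasibility considerations". It then links attrition to the evaluable number: "Assuming 20% attrition, we aim to enroll 24 participants to ensure at least 10 evaluable participants per arm". The section on randomization and allocation concealment confirms equal arms: "Participants will be randomized in a 1:1 ratio".

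Under Feasibility outcomes, the second progression criterion is "retention rate of 80% or higher (i.e., at least 20 of 24 participants completing the study" (the parenthesis closes there). The fourth is "assessment completion rate of 90% or higher for the primary outcome". Of the whole set the article says: "These criteria will determine whether progression to a full-scale confirmatory trial is warranted".

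The primary outcome is measured at week 12, and the last follow-up is at week 24. The article does not say by which week the 20% attrition is expected to have occurred.

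**The concern.** The Sample size sentence offers a guarantee, yet its own inputs give fewer than 10 per arm. A reader planning around it, for example to judge how precisely the standard deviation will be estimated, would take 10 per arm as a floor when it lies slightly above the expected value.

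The assumed loss of 20% is also exactly the complement of the 80% retention required for progression. Participants come in whole numbers, so 80% of 24 (19.2) becomes a requirement of 20. The plan therefore expects a result marginally below its own bar. At stake are a correct statement of the evaluable size and a realistic expectation of whether the retention criterion will be met.

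**Working it through.** **Inputs.** Enrolment 24, 12 per arm, 20% attrition, target of at least 10 evaluable per arm (Sample size); 1:1 allocation (Randomization and allocation concealment); retention limit of 20 of 24 (Feasibility outcomes). Assumption added here: participants drop out independently with the same probability *d*.

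**1. Reproducing the plan's figure.**
- Multiplying up: 10 × (1 + 0.20) = 12 per arm, 24 in total. This matches the stated enrolment and may be where it came from, though the article does not show its calculation.
- Dividing by the fraction retained, which is the correct inflation: 10 / (1 − 0.20) = 12.5, so 13 per arm, 26 in total.

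The two differ by 2 enrolled participants.

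**2. Expected evaluable number.**
- Per arm: 12 × 0.8 = 9.6.
- In total: 24 × 0.8 = 19.2.
- Largest attrition compatible with 10 of 12: 2/12 = 16.7%.

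**3. Chance of at least 10 per arm at *d* = 0.20.** With X ~ Binomial(12, 0.8):

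P(X ≥ 10) = 66 × 0.8¹⁰ × 0.2² + 12 × 0.8¹¹ × 0.2 + 0.8¹² = 0.283 + 0.206 + 0.069 = 0.558.

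For both arms: 0.558² = 0.312 (0.31).

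**4. Chance of meeting the retention criterion.** With Y ~ Binomial(24, 1 − *d*), P(Y ≥ 20):

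| Attrition *d* | P(at least 20 of 24) |
|---|---|
| 20% | 0.460 |
| 19% | 0.510 |
| 16.7% | 0.629 |
| 15% | 0.713 |
| 10% | 0.915 |

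The probability crosses 0.5 at attrition of about 19.2%.

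**The case against.** The strongest reply is that the gap is trivial. It is 0.4 participant per arm in a pilot whose size rests on feasibility, with all efficacy comparisons declared exploratory. No power figure changes. This stands, and it limits the point to a correction of wording.

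A second reply is that 31% is a harsh test. Inflating for expected dropout never guarantees a number in both arms; even 13 per arm would reach 10 in both with probability of only about 56%. This also stands: much of the 31% is ordinary binomial scatter. But the article chose a word that promises a minimum, and the expected value alone already falls short of it.

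Third, the article describes measures to limit dropout (flexible scheduling, make-up sessions, travel reimbursement), so 20% may be a cautious allowance, and the retention result reverses with one percentage point less attrition. That is fair. The retention criterion is finely balanced; it is not expected to fail by any clear margin. A single pass/fail cut is also a legitimate progression rule.

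A reader might go further and infer that the 90% assessment-completion criterion is likely to fail, or that it makes the retention criterion redundant. The article does not support this. The inference needs all 24 as the denominator (so 22 assessed) and the whole 20% lost by week 12; only then is the pass probability about 11%. Neither condition is stated. If the loss accrues at a constant rate to week 24, about 10.6% is lost by week 12 and the pass probability is about 53%, even with 24 as denominator. If the denominator is those still in follow-up, attrition does not decide the result. Nor are the criteria redundant: 22 participants could be assessed at week 12 and 3 of them lost by week 24, leaving 19, which meets one criterion and fails the other. The unstated denominator is a detail that an article may leave to the full protocol.

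**Conclusion.** The point holds as an arithmetic and wording fault of minor consequence. At the plan's own 20%, the evaluable number is 9.6 per arm on average, and at least 10 is reached with probability about 56% in one arm and 31% in both. The retention limit coincides with the planning rate and would be met about 46% of the time at 20%, 51% at 19% and 71% at 15%. It would be too strong to conclude that a pilot running to plan will clearly be told not to progress.

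The probabilities rest on independent dropout at a common rate. The 9.6 takes the sentence as it reads, with the 20% applied to the 12 per arm to obtain the evaluable number. If instead the 20% were meant to accrue evenly to week 24 and evaluability were judged at week 12, the average would be 12 × 0.894 = 10.7 per arm. The chance of 10 in both arms would then lie between 67% (12.5% attrition) and 79% (10% attrition), which is still not assurance. The sentence says nothing of the kind.

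**What to change.** In the Sample size section, replace the sentence with wording such as: *24 enrolled with 20% attrition gives about 19 evaluable (9–10 per arm); 10 per arm requires attrition of at most 16.7%.* Drop the word *ensure*.

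Add a short acknowledgement, there or under Feasibility outcomes, that the planning attrition equals the retention limit, so the retention criterion is close to a coin toss at the assumed rate and becomes comfortable only if attrition is lower.

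Enrolment, the progression criteria and the analysis can stay as they are. The cost is two sentences and a slightly less favourable stated evaluable number. The article reports that no participants had been enrolled when it was written, so the text can be corrected before recruitment begins.

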### Statistical analysis

All analyses will follow the intention-to-treat (ITT) principle, defined as all randomized participants who receive at least one treatment session and have at least one post-baseline assessment. Continuous variables will be summarized as mean and standard deviation (or median and interquartile range where appropriate). Between-group comparisons for the primary outcome (UEMS change from baseline to week 12) will be analyzed using a linear mixed-effects model with treatment group, time, and treatment-by-time interaction as fixed effects, stratification factors (AIS grade and baseline UEMS) as covariates, and participant as a random effect. An unstructured covariance matrix will be assumed for repeated measures.

Secondary continuous outcomes will be analyzed using analogous mixed-effects models. Effect sizes (Cohen d) and 95% confidence intervals will be reported for all between-group comparisons to support the planning of a future definitive trial. A per-protocol analysis (participants completing 20 or more of 24 sessions) will be conducted as a sensitivity analysis. Missing data will be handled within the mixed-effects framework under the assumption of missing at random (MAR). Feasibility outcomes will be reported descriptively against the pre-specified progression criteria. A sensitivity analysis excluding participants with antispasticity dose changes will be conducted for the Modified Tardieu Scale outcome. Safety outcomes will be tabulated by treatment group with frequencies and proportions. All analyses will be performed using R (version 4.3 or later), with statistical significance set at P < .05. All between-group efficacy comparisons (primary and secondary) will be reported as exploratory. The trial’s primary purpose is estimation of effect sizes, variability, and feasibility parameters for a definitive trial. Secondary functional and neurophysiological outcomes carry elevated Type I error risk due to multiple testing without correction and should be interpreted as hypothesis-generating only.

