**Methods:**

This single-center, two-arm, assessor-blinded, pilot randomized controlled trial will enroll 24 adults aged 21–65 years with chronic (more than 12 months post-injury) incomplete cervical SCI (American Spinal Injury Association Impairment Scale grade C or D, neurological level C2 to C8) at Alexandra Hospital, Singapore. Participants will be randomized 1:1 to receive either iTBS combined with tSCS plus standardized upper limb rehabilitation or tSCS plus upper limb rehabilitation alone. Interventions will be delivered twice weekly for 12 weeks (24 sessions). The primary outcome is the change in Upper Extremity Motor Score from baseline to 12 weeks. Secondary outcomes include measures of upper limb function, independence, spasticity, corticospinal excitability, quality of life, and goal attainment. Assessments will be conducted at baseline, post-intervention, and at 4- and 12-week follow-up.

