### Blinding

This trial employs an assessor-blinded design in which outcome assessors are blinded to treatment allocation. A dedicated, unblinded intervention therapist will be responsible for delivering iTBS and configuring tSCS at each session and will have no involvement in outcome assessment. Participants in the control arm will be aware that they are not receiving iTBS, as the brief nature of the iTBS procedure and the characteristic scalp sensation make participant-level sham impractical in this pilot study. To mitigate expectation effects, both arms will be framed during consent as “active neuromodulation combined with rehabilitation” with no comparative ranking. Both groups receive identical therapist contact time, session structure, and rehabilitation content. The Credibility/Expectancy Questionnaire will be administered at baseline and week 2 and entered as a covariate in sensitivity analyses of the primary outcome. However, assessor blinding will be rigorously maintained through physical separation of intervention delivery and outcome assessment areas within the rehabilitation department. The success of assessor blinding will be formally evaluated using a blinding questionnaire at week 12 and week 24. Bang’s Blinding Index will be used, a validated metric ranging from minus 1 (opposite guessing) to +1 (complete unblinding), with 0 indicating random guessing. If Bang’s Blinding Index exceeds 0.2 with 95% CI excluding zero, a pre-planned sensitivity analysis will re-analyze the primary outcome using only objective/instrumented measures (grip/pinch dynamometry, Nine-Hole Peg Test, Box and Block Test, and neurophysiological parameters), and an independent second assessor will re-score a random 30% sample of ISNCSCI examinations from video recordings.

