#### Secondary outcomes

Secondary clinical and neurophysiological outcomes are summarized in Table 2.

**TABLE 2 T2:** Secondary outcome measures.

Outcome measure	Description	Domain	Timepoints
GRASSP-2	Graded Redefined Assessment of Strength, Sensibility and Prehension version 2; comprehensive UE impairment measure for tetraplegia	Motor/Sensory	Wk 0, 12, 16, 24
Grip/pinch strength	Maximal grip force (Jamar dynamometer), lateral pinch, tip pinch, and tripod pinch (pinch gauge)	Motor	Wk 0, 12, 16, 24
Nine-Hole Peg Test	Timed fine motor dexterity assessment	Fine Motor	Wk 0, 12, 16, 24
Box and Block Test	Gross manual dexterity (blocks transferred in 60 s)	Gross Motor	Wk 0, 12, 16, 24
CUE-T	Capabilities of Upper Extremity Test; objective functional assessment for tetraplegia	Function	Wk 0, 12, 16, 24
SCIM-III	Spinal Cord Independence Measure III; self-care, respiration, sphincter management, mobility	Independence	Wk 0, 12, 16, 24
Modified Tardieu Scale	Velocity-dependent spasticity of elbow and wrist flexors/extensors	Spasticity	Wk 0, 6, 12, 16, 24
CMCT	CMCT per IFCN guidelines: CMCT = MEP latency minus PCT, where PCT = (F-latency + M-latency minus 1) / 2	Neurophysiology	Wk 0, 12, 16, 24
MEP parameters	Amplitude, latency, resting and active motor thresholds from FDI and APB	Neurophysiology	Wk 0, 12, 16, 24
EMG	Surface electromyography from key upper limb muscles during standardized tasks	Neurophysiology	Wk 0, 12, 16, 24
EQs-5D-5L	Generic health-related quality of life; utility index and visual analog scale	Quality of Life	Wk 0, 12, 24
Modified GAS	Patient-identified goals scored on a standardized attainment scale	Patient-Centered	Wk 0, 12, 16, 24
Adverse events	Structured adverse event recording at every session	Safety	Every session

GRASSP-2, Graded Redefined Assessment of Strength, Sensibility and Prehension version 2; CUE-T, Capabilities of Upper Extremity Test; SCIM-III, Spinal Cord Independence Measure III; CMCT, central motor conduction time; MEP, motor evoked potential; FDI, first dorsal interosseous; APB, abductor pollicis brevis; EMG, electromyography; GAS, Goal Attainment Scale; Wk, week.

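### The one analysis set stated for all analyses requires a post-baseline assessment, so safety tables built on it can omit treated participants who had an adverse event and left before any assessment

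*Protocol article*

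**What the plan says.** The protocol's Statistical analysis section begins with a rule of general scope: "All analyses will follow the intention-to-treat (ITT) principle". It then fixes the population as "defined as all randomized participants who receive at least one treatment session and have at least one post-baseline assessment".

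Later in the same section it plans the safety analysis: "Safety outcomes will be tabulated by treatment group with frequencies and proportions". It names no safety population, denominator or exception for these tables. It does name other departures from the main set: a per-protocol analysis, and a sensitivity analysis for the Modified Tardieu Scale without participants whose antispasticity dose changed.

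On timing, Table 2 (Secondary outcomes) has "Structured adverse event recording at every session". For outcome visits the abstract states: "Assessments will be conducted at baseline, post-intervention, and at 4- and 12-week follow-up". Table 2 adds a week 6 measurement for the Modified Tardieu Scale only. The Blinding section adds a questionnaire: "The Credibility/Expectancy Questionnaire will be administered at baseline and week 2".

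Safety is part of the primary objective and is also secondary objective 3. The fifth progression criterion under Feasibility outcomes is "no serious adverse events attributable to the combined intervention".

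**The concern.** A safety table should count everyone exposed to the intervention. The stated set adds a second condition, an assessment after baseline, and that condition can depend on tolerability. A participant who is stimulated, has an adverse event, leaves and does not return meets the first condition and fails the second. The event is on the case report form, but the participant is in neither the numerator nor the denominator of the table.

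The people lost this way would tend to be those who tolerated stimulation least, so the error would usually make the intervention look safer. With 12 participants per arm, each one omitted changes the reported proportion visibly, and safety is one of the trial's main aims.

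This is not a complaint that the article leaves out a safety population, which an analysis plan could supply. The article states a population for every analysis, and that population does not suit safety.

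**Working it through.** **Inputs from the protocol**
- Size: "the sample size of 24 participants (12 per group) is based primarily on feasibility considerations" (Sample size).
- Attrition: 20%, with at least 10 evaluable per arm intended (Sample size).
- Sessions: twice weekly for 12 weeks, 24 in total (Interventions, Overview).
- Post-baseline measurements: week 2 (questionnaire), week 6 (Modified Tardieu Scale), and weeks 12, 16 and 24 (most other outcomes).

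**The plan's own figure.** Inflating 10 per arm by n × (1 + d) gives 10 × 1.2 = 12, or 24 in total, which is the stated number. Dividing by (1 − d) gives 10 / 0.8 = 12.5, so 13 per arm. Taking 20% off 12 leaves 12 × 0.8 = 9.6. The stated size is therefore close to its aim, and the attrition allowance is 12 × 0.2 = 2.4, about 2 participants per arm.

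**How long a participant can be exposed before qualifying.** At two sessions a week:
- until week 2: 2 × 2 = 4 sessions, if the questionnaire counts as an assessment;
- until week 6: 2 × 6 = 12 sessions, if only clinical outcomes count;
- until week 12: 2 × 12 = 24 sessions, if the week 6 spasticity measure is missed or not counted.

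**Effect on a reported proportion.** Let k participants in one arm of 12 have an adverse event and leave with no post-baseline assessment, with no other events in the arm. All treated gives k/12; the stated set gives 0/(12 − k). The values of k are assumptions. Intervals are exact (Clopper-Pearson) 95%.

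| k | All treated | Stated set |
|---|---|---|
| 1 | 1/12 = 8.3% (0.2 to 38.5) | 0/11 = 0% (upper limit 28.5) |
| 2 | 2/12 = 16.7% (2.1 to 48.4) | 0/10 = 0% (upper limit 30.8) |
| 3 | 3/12 = 25.0% (5.5 to 57.2) | 0/9 = 0% (upper limit 33.6) |

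With one further event among those who stay, k = 1 gives 2/12 = 16.7% against 1/11 = 9.1%, and k = 2 gives 3/12 = 25.0% against 1/10 = 10.0%.

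**Direction.** The bias is downward only when those omitted had events more often than those kept. If one early leaver had no event and one participant who stayed did, the stated set gives 1/11 = 9.1% against 1/12 = 8.3%, slightly too high. Withdrawal because of an adverse event is the case that makes the table too favourable.

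**The case against.** The best defence is that the opening sentence cannot be literal for everything in its section. Retention is judged as 20 of 24 participants, which cannot be computed in a set that already requires an assessment. The sentence may be a loose statement of the efficacy principle, with the safety set left to the analysis plan. That is plausible as to intent. But the section uses a narrower term when it means efficacy comparisons only, and lists its other exceptions without listing safety. An analysis plan could put this right only by departing from the published text.

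A second defence is that adverse event recording at each session is itself a post-baseline assessment, so every treated participant qualifies. The term is undefined, and adverse events do appear in the outcome table. On that reading, however, the second condition would exclude nobody, and it does not match the abstract's use of the word for the scheduled outcome visits.

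Third, the independent monitoring committee reviews safety after 8 and 16 enrolments, and no analysis set restricts what it sees. That protects participants during the trial. It does not set the denominator of the reported tables.

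Two stronger readings are tempting, and the documents do not support them. A reader might infer that anyone who stops stimulation because of an adverse event drops out of the safety tables. That is not so: attending any later assessment keeps the participant in. A reader might also infer that the trial could count no attributable serious events and recommend progression while one had occurred in an early leaver. The fifth progression criterion is a plain count with no denominator and no analysis set, and the retention criterion in the same list counts out of all 24. Read on its own terms, one attributable serious event in any treated participant fails it. The general wording in the Statistical analysis section leaves the point open, and no more.

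**Conclusion.** The concern holds for the safety tables. Followed as written, the plan leaves out a treated participant who has a recorded adverse event but no post-baseline assessment, and so can understate the event proportion. One such participant in an arm changes 8.3% to 0%. Two, about the number the attrition allowance provides for, change 16.7% to 0%.

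These sizes are illustrations. The protocol gives neither the timing nor the cause of its 20% attrition, and no rate of early withdrawal for adverse events. All of the attrition could fall after week 12, and then nothing would be lost. If the week 2 questionnaire counts as an assessment, the exposed period shrinks to roughly the first two weeks.

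The point does not show that the go/no-go decision would be wrong, since the criterion on serious events is not tied to this set. It should be fixed, because safety is a main aim, withdrawals for adverse events push the result in the favourable direction, and the remedy is simple.

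**What to change.** In the Statistical analysis section, limit the stated population to efficacy analyses. Add that safety tables include all participants who received any study stimulation, grouped by treatment received, with no condition on later assessments. For clarity, say that the count for the fifth progression criterion uses the same participants.

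The cost is one sentence. No new data are needed, because adverse events are already recorded at each session, and the protocol reports that nobody had been enrolled when it was written. The reported event proportion may come out slightly less favourable.

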### Interventions

#### Overview

Both arms will receive individualized tSCS combined with standardized upper limb rehabilitation. The experimental arm will additionally receive iTBS immediately prior to each rehabilitation session. Interventions will be delivered twice per week for 12 weeks, yielding a total of 24 sessions. A minimum of 20 completed sessions (83%) will be required for per-protocol analysis.

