### Study schedule

#### Data collection and management

The schedule of enrollment, interventions, and assessments is presented in Table 3. Clinical outcomes will be assessed by trained, certified assessors who are blinded to group allocation and have demonstrated inter-rater reliability (intraclass correlation coefficient of 0.85 or higher) on the ISNCSCI examination. All data will be collected using electronic case report forms (eCRFs) hosted on a secure REDCap database maintained by the Clinical Research & Innovation Office, Tan Tock Seng Hospital, with automated range checks, audit trails, and role-based access control. Neurophysiological data (MEPs, CMCT, EMG) will be recorded using a dedicated EMG system and processed semi-automatically with manual verification by a blinded neurophysiologist. All data will be backed up daily and stored on encrypted institutional servers in compliance with Singapore’s Personal Data Protection Act (PDPA) and the HBRA.

**TABLE 3 T3:** SPIRIT schedule of enrollment, interventions, and assessments.

Timepoint	Screen	Baseline (Wk 0)	Intervention (Wk 1-12)	Post-Tx (Wk 12)	FU1 (Wk 16)	FU2 (Wk 24)
Informed consent	X					
Eligibility assessment	X					
Medical history	X					
Surgeon clearance	X					
Randomization		X				
iTBS (experimental arm)			2x/wk			
tSCS (both arms)			2x/wk			
UL rehabilitation (both arms)			2x/wk Wk 6 Each visit			
ISNCSCI / UEMS		X		X	X	X
GRASSP-2		X		X	X	X
Grip/Pinch strength		X		X	X	X
Nine-Hole Peg Test		X		X	X	X
Box and Block Test		X		X	X	X
CUE-T		X		X	X	X
SCIM-III		X		X	X	X
Modified Tardieu Scale		X		X	X	X
CMCT and MEP assessment		X		X	X	X
EMG		X		X	X	X
EQ-5D-5L		X		X		X
Modified GAS		X		X	X	X
Adverse events				X	X	X
Blinding assessment				X		X

ISNCSCI, International Standards for Neurological Classification of Spinal Cord Injury; UEMS, Upper Extremity Motor Score; GRASSP-2, Graded Redefined Assessment of Strength, Sensibility and Prehension version 2; CUE-T, Capabilities of Upper Extremity Test; SCIM-III, Spinal Cord Independence Measure III; CMCT, central motor conduction time; MEP, motor evoked potential; EMG, electromyography; GAS, Goal Attainment Scale; FU, follow-up; Wk, week; UL, upper limb.

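### The set called intention-to-treat is a modified ITT set that has no UEMS between baseline and week 12, and the mixed model carries one covariance parameter too many

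*Protocol article*

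**What the plan says.** All references are to the protocol article.

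- **Analysis set (Statistical analysis).** All analyses are said to follow intention-to-treat, with the set "defined as all randomized participants who receive at least one treatment session and have at least one post-baseline assessment".
- **Model (Statistical analysis).** The primary outcome is UEMS change from week 0 to week 12. The fixed effects are group, time and their interaction, with "stratification factors (AIS grade and baseline UEMS) as covariates, and participant as a random effect". The next sentence adds: "An unstructured covariance matrix will be assumed for repeated measures".
- **Missing data (Statistical analysis).** These are left to the mixed model under missing at random (MAR). The named sensitivity analyses are a per-protocol analysis and, for the Modified Tardieu Scale only, exclusion of participants with antispasticity dose changes. The Blinding section adds sensitivity analyses for expectancy and for failed assessor blinding. None of them addresses informative loss.
- **Visits (Table 3).** UEMS is taken at weeks 0, 12, 16 and 24. Table 2 puts a Modified Tardieu assessment at week 6.
- **Session completers (Interventions, Overview).** "A minimum of 20 completed sessions (83%) will be required for per-protocol analysis"
- **Attrition (Sample size; Feasibility outcomes).** 20% attrition is assumed without a time point. Retention is defined by completing the study, with 20 of 24 as the criterion.
- **Blinding.** Control participants will know that they do not receive iTBS.

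**The concern.** Intention-to-treat protects the comparison because membership is fixed at randomisation. Here it depends on two later events: starting treatment and returning for an assessment. Participants know their arm, so both events could depend on allocation. For example, a control participant may lose interest on learning that iTBS is not given, or an experimental participant may stop because the added procedure brings no visible gain.

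The visit schedule sharpens this. A MAR mixed model protects against dropout to the extent that earlier measurements predict the missing one. With no UEMS between weeks 0 and 12, someone lost in that interval brings only a baseline value.

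The model statement adds a separate difficulty. A participant random effect and an unstructured covariance both describe within-participant correlation. It is also unclear whether week 0 is a level of time, and so a response, or enters only through the baseline covariate. Both choices could end up being made after the data are seen.

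At stake is the effect estimate. The protocol says that the trial exists mainly to supply effect sizes, variability and feasibility figures for a definitive trial.

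**Working it through.** **1. The plan's own figure.** Inputs: 24 enrolled, 20% attrition, at least 10 evaluable per arm (Sample size).

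- 20 × (1 + 0.2) = 24, the stated number. Dividing instead gives 20 / (1 − 0.2) = 25, or 10 / 0.8 = 12.5, rounded up to 13 per arm and 26 in all. The stated 24 is within two of each, and it is not disputed here.
- Attrition of 20%: 24 × 0.20 = 4.8 lost, and 24 × 0.80 = 19.2 remaining, or 9.6 per arm.

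**2. Who supplies a post-baseline UEMS.**

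| Participant | In the plan's set? | Post-baseline UEMS? |
|---|---|---|
| Randomised, no session | No | Not used, even if collected |
| Treated, lost before any post-baseline assessment | No | None |
| Treated, week-6 Tardieu, then lost | Yes, as worded | None |
| Stops sessions, attends week 12 | Yes | Yes |
| Misses week 12, attends week 16 or 24 | Yes | Yes, contributes under MAR |
| Lost after week 12 | Yes | Yes |

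The primary analysis thus rests on participants with at least one UEMS at week 12 or later. The 4.8 is a ceiling on those lost without one. It is reached only if every loss precedes week 12.

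**3. Size of a possible bias.** The protocol gives no dropout rates by arm and no SD, so everything here is assumed. Let a fraction p of an arm be lost, with a mean change d points below that of those retained. The retained mean then exceeds the full-arm mean by p × d, and the shift in the effect is p(exp) × d(exp) − p(ctl) × d(ctl).

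- Loss of 33% control and 8% experimental, d = 2 in both: 0.08 × 2 − 0.33 × 2 = 0.16 − 0.66 = −0.50. The effect is understated by 0.5 points, a quarter of the 2-point difference in the Hypotheses section.
- Loss of 30% control and 10% experimental, d = 1 to 2: understated by 0.2 to 0.4.
- Loss of 20% experimental with d = 2 to 4, and no such gap in controls: overstated by 0.4 to 0.8.
- Equal rates and equal gaps in both arms: no shift.

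A large-sample simulation (assumed baseline SD 4, residual SD 3, true effect 2) gave a baseline-adjusted effect of 2.00 when loss depended on baseline and arm (MAR, 81% kept). It gave 2.82 when poor responders left the experimental arm (76% against 83% kept).

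**4. Covariance.** As written, V = s²J + R, where J is a matrix of ones and R is unstructured. T visits give T(T + 1)/2 distinct elements of V.

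- Four visits: 10 elements, 10 + 1 = 11 parameters, rank 10.
- Three visits: 6 elements, 7 parameters, rank 6.
- Unstructured alone: 10 parameters at rank 10, or 6 at rank 6.

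There is exactly one surplus parameter. Any s² that leaves R = V − s²J a valid covariance matrix gives the same V. In an illustrative data set, s² = 0, 2, 4 and 5.5 all gave log-likelihood −111.646, treatment contrast 0.838 and SE 0.913. The split between s² and R is undetermined; V and the treatment contrast are not.

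**The case against.** The strongest defence has five parts.

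- **The set is inclusive.** One session is enough to enter, and session completers form a separate per-protocol set. A reader might infer that the primary analysis is completers-only. The documents do not support that: people who stop treatment but attend at week 12, 16 or 24 are kept. This part stands.
- **Attrition has no date.** A reader might infer that about five participants will leave the set. Retention is defined by completing a study that runs to week 24, and any post-baseline assessment qualifies, including the week-6 Tardieu. The 4.8 is only an upper limit. This stands.
- **MAR may hold.** If it does, the baseline-adjusted estimate is sound, and adding back participants with only a baseline value contributes almost nothing on the treatment effect. This stands, and it means that relabelling alone does not cure informative loss.
- **The treatment effect is identified.** A reader might infer that the model cannot be fitted or that the primary contrast is undefined. Only the variance split is affected, and the random effect may simply be a loose way of naming the clustering unit. This largely stands, although software may still fail to converge or report arbitrary components.
- **Detail belongs in the SAP, and efficacy is exploratory.** Degrees of freedom and fallback structures can indeed wait. Baseline UEMS also has a natural reading as the randomisation stratum (10–14 versus 15–20). Nor does the article say that assessments stop with treatment. The exploratory label lowers the severity, but it does not excuse a wrong name for the set or a redundant term, both of which the article states outright.

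**Conclusion.** The point holds in limited form. The set is modified ITT under an ITT label. The UEMS analysis depends on attendance at week 12 or later, with no interim UEMS for anyone lost sooner (at most about 4.8 of 24). No planned analysis tests departure from MAR.

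Whether bias results, in which direction and how large, is unknown. The illustrations run from 0.5 points of understatement to 0.8 of overstatement against a 2-point target. They rest on assumed loss rates and gaps and on loss that is not at random; under MAR the bias vanishes.

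The covariance specification has one surplus parameter (11 against rank 10 at four visits). The consequence is an arbitrary variance split and possible non-convergence, not an inestimable treatment effect.

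Should-fix: efficacy is declared exploratory, but the effect estimate is a main product of this pilot.

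**What to change.** 1. Define ITT as all randomised participants, analysed as allocated. Rename the present set modified ITT and keep it as a sensitivity analysis.
2. State that UEMS is collected at weeks 12, 16 and 24 whether or not sessions continue. This does most to reduce the problem.
3. Add a simple delta-adjusted analysis for missing week-12 UEMS: impute under MAR, shift the imputed values over a stated range separately by arm (for example 0 to 2 points lower), and report how the week-12 difference moves. This also brings all 24 participants into an analysis.
4. Keep the unstructured covariance and drop the participant random effect.
5. Treat week 0 either as a response or as a covariate, not both. As a response, with a common baseline mean across arms, everyone with a baseline enters the model. As a covariate, those with no later UEMS fall out of the likelihood whatever the set is called, so item 3 is then needed to represent them.

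The cost is wording, a little extra analysis, and a few visits by participants who have stopped treatment. The Results section reports that no one has been enrolled, so every change can be made before recruitment.
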